#### Randomization

Once study eligibility, consent, and baseline assessment are completed, subjects will be randomized using a web-based randomization tool (DACIMA 3.3.8) [23] in a 1:1 ratio on the day of surgery to either mild or moderate hypothermia strategies during aortic hemiarch surgery with uSACP. Block randomization to each treatment arm will be used across participating centres.

In order to ensure a normal distribution of kidney function among patients in both treatment arms, stratified randomization will be performed based on two eGFR ranges: 30–59 ml/min/1.73m^2^ and ≥ 60 ml/min/1.73m^2^ [24]. Randomization will also be stratified by site to reduce possible confounding from differences in standard of care practices across sites.

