#### Sample size

Taking into consideration the aforementioned incidence rates of both neurologic injury and AKI, a composite outcome of ~ 35% should represent the incidence of these injuries in patients undergoing hemiarch surgery using traditional methods of hypothermia. This accounts for a 5–10% overlap that will likely exist, where a patient will suffer both types of injuries.

We hypothesize that circulatory arrest using mild hypothermia (32 °C) and uSACP during aortic hemiarch surgery will result in a 15% absolute risk reduction in composite outcomes (neurologic injury and AKI) from 35% to 20%. With an alpha (type 1 error) of 0.05 and power of 80%, and a 5% loss to follow-up, approximately 141 subjects will be needed in each group for a total of a 282 patients.

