#### Statistical analysis

The trial will be analyzed on a true intention to treat (ITT) basis, including all trial participants who were randomized regardless of adherence to treatment protocol, including those who are lost to follow-up or may have died. Patient crossover will be tracked and reported with the final trial results. In addition, a ‘modified ITT’ analysis will be performed (excluding patients not assessed for the primary outcome or lost to follow-up and/or early death) to account for potential biases introduced with ITT analyses.

The primary endpoint of our composite outcome will be evaluated using a chi squared test (or Fisher’s exact test if cell count is < 5 in any cell). Categorical secondary endpoints will be analyzed in the same method, while continuous secondary endpoints will be analyzed using Students *t*-test (or Wilcoxon rank sum test if the data are not normally distributed). Continuous variables will be reported as mean ± standard deviation or median (interquartile range [IQR]) for non-normally distributed variables. Categorical variables will be reported as counts and percentages. As the primary outcome is a composite of both neurologic and AKI, secondary outcome analysis will pay particular attention to individual assessment of these indices for treatment effect and positive correlation.

Exploratory multivariable logistic regression analysis will be performed to determine risk factors for neurologic and renal complications post-operatively. A *p* value of < 0.05 will be considered statistically significant. Multivariable analysis will include variables with *p* <  0.20 in univariate analysis in addition to clinically significant variables.

Once data collection is complete for all study participants, a statistical analysis plan (SAP) will be created prior to data analysis and release of results. As the principle statistician involved in this trial, [name] (PhD) will primarily be responsible for this analysis. [name] is the Director of the Cardiovascular Research Methods Centre at the UOHI and Professor in the School of Epidemiology, Public Health and Preventive Medicine at the University of Ottawa.

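### Randomization is stratified by eGFR and site but the primary chi-squared test ignores both; using the strata would be a free efficiency gain, not the repair of an error

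*Protocol article*

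**What the plan says.** Under Randomization, the protocol article states that "stratified randomization will be performed based on two eGFR ranges" (30–59 and ≥ 60 ml/min/1.73m²), with the aim of similar kidney function in the two arms. It adds: "Randomization will also be stratified by site to reduce possible confounding from differences in standard of care practices across sites". Four centres take part, so there are 2 × 4 = 8 strata.

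Under Statistical analysis, the test is fixed: "The primary endpoint of our composite outcome will be evaluated using a chi squared test", replaced by Fisher's exact test when any cell count is below 5. Categorical secondary endpoints are handled in the same way. The only multivariable model is an exploratory logistic regression to find risk factors, with candidates screened at univariate p < 0.20. It is not an adjusted comparison of the arms. No other section provides a stratified or adjusted treatment comparison.

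The SAP is to be written once data collection is complete and before the analysis.

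**The concern.** Stratified allocation largely removes chance imbalance between the arms in eGFR range and site. The pooled chi-squared variance still counts the outcome variation between strata as if it could differ by chance between arms. When the strata are prognostic, the standard error is therefore larger than the true sampling variation of the risk difference. The test then runs below its nominal 5% level, and an analysis that used the strata would have more power.

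This is plausible here because AKI is one of the two components of the composite and the larger one expected (25%, against 15–20% for neurologic injury). Baseline kidney function may well predict it. The site stratification is itself justified by expected differences in care. At stake is some extra power that could be had without further patients.

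**Working it through.** **Step 1. The plan's own sample size.** Inputs from Sample size: 35% vs 20%, "With an alpha (type 1 error) of 0.05 and power of 80%, and a 5% loss to follow-up", 1:1 allocation. Sidedness is not stated. Two-sided is assumed, because a one-sided test gives 115 per arm after dropout and does not fit 141. With unpooled variance:

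n = (1.960 + 0.842)² × (0.35 × 0.65 + 0.20 × 0.80) / 0.15² = 135.2 per arm.

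Allowing for 5% loss: 135.2 × 1.05 = 141.9, or 135.2 / 0.95 = 142.3. The stated 141 per group (282 in total) reproduces to within about 1%. Evaluable patients: 282 × 0.95 ≈ 268, or 134 per arm. The usual two-proportion power formula gives 78.8% at 134 per arm and 80.9% at 141.

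**Step 2. Why the test is conservative.** The pooled variance splits into a within-stratum and a between-stratum part:

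p(1 − p) = mean of p_h(1 − p_h) + variance of p_h across strata.

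Stratified allocation removes the second part from the true variance of the difference, but the chi-squared test keeps it. As a hand check with eGFR alone, assume 25% of patients at eGFR 30–59, an odds ratio of 3 and an overall risk of 35% in both arms (no treatment effect). The stratum risks are then about 28.5% and 54.5%, since 0.75 × 0.285 + 0.25 × 0.545 = 0.35.

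- Between-stratum variance: 0.75 × 0.25 × (0.545 − 0.285)² = 0.0127.
- Total variance: 0.35 × 0.65 = 0.2275, so the share removed is 5.6%.
- Effective critical value: 1.96 / √(1 − 0.056) = 2.017, a true type I error of about 4.4%.

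**Step 3. Simulation with both factors.** The set-up was 268 evaluable patients, permuted blocks of 4 within eGFR × site, and 100,000 trials per scenario, comparing Pearson chi-squared with CMH over the 8 strata. Site shares of about 36/21/21/21% follow from the enrolment forecast in the Discussion. The remaining inputs are assumptions, because the documents do not give them: 15% or 25% of patients at eGFR 30–59, the eGFR odds ratio (OR), and the spread of sites as a standard deviation (SD) on the log-odds scale. Ranges cover the two eGFR shares.

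| Assumed strength | Type I error, chi-squared | Type I error, CMH | Power, chi-squared | Power, CMH |
|---|---|---|---|---|
| None (OR 1, SD 0) | 5.1% | 5.1% | 79.2% | 78.9% |
| OR 1.5, SD 0.2 | 4.8–4.9% | 4.9–5.1% | 79.5–79.7% | 79.6–79.8% |
| OR 2, SD 0.3 | 4.6% | 5.0% | 79.9% | 80.6–80.7% |
| OR 3, SD 0.3 | 4.3–4.4% | 5.0% | 80.0% | 81.1–81.7% |
| OR 3, SD 0.5 | 3.9–4.2% | 4.9–5.1% | 80.2–80.7% | 82.3–83.0% |
| OR 4, SD 0.7 | 3.4% | 5.0% | 80.9–81.3% | 84.5–85.2% |

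The row for OR 3 and SD 0.3 agrees with the hand check once a small site contribution is added. Chi-squared power does not fall as the strata become more prognostic. Stratified allocation lowers the true variance of the difference, and that slightly more than offsets the oversized standard error.

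**Step 4. The Fisher rule.** Take a hypothetical rare endpoint with 3/141 vs 10/141 events. The expected count is 13 / 2 = 6.5 events per arm, so the usual condition for chi-squared is met, yet the observed 3 triggers Fisher. Pearson gives p = 0.047 and Fisher p = 0.085. For the primary endpoint the rule has no bearing: even 20% of 134 is about 27 events.

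**The case against.** The strongest reply is that nothing planned is lost. The sample size and the chi-squared test agree with each other, and the test gives 79% to 81% power in every scenario. That stands. A reader might infer that the trial falls short of its 80% power, but the figures do not support it: what is forgone is additional power.

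Second, the type I error is at or below 5%. A reader might infer that a significant result could not be trusted. The opposite holds, since a conservative test leaves such a result valid. Nor is there a mismatched confidence interval, because the article specifies none for the primary comparison.

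Third, the size rests on assumptions. The Randomization section gives balance and possible confounding as its reasons. It does not say that eGFR or site drives the composite, or how strongly. The 4-point gain needs an odds ratio of 4 together with large site differences; at an odds ratio of 2 and SD 0.3 the gain is under 1 point. This also stands, and the point must be put conditionally.

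Fourth, adjusted estimates are often left to the SAP. This carries less weight, because the article names the primary test instead of leaving it open. The SAP is also due only after data collection, when a change of primary test could look data-driven.

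Last, the Fisher rule is minor. Cell count is common shorthand, Fisher's test is valid when used, and the example was chosen to straddle 0.05.

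**Conclusion.** The mismatch between stratified randomization and an unstratified primary test is in the text, and the direction of its effect is certain if the strata are prognostic. For assumed eGFR odds ratios of 2 to 4 with site differences, the chi-squared test has a type I error of about 3.4% to 4.6% against about 5% for CMH, and forgoes roughly 1 to 4 power points. A repeat with 266 to 268 evaluable patients and 40,000 trials per scenario gave about 3.0% to 4.5% and 0.7 to 4 points. With non-prognostic strata the type I errors are equal and CMH costs at most 0.3 points.

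This is an opportunity to gain efficiency at no cost in patients. It is not a validity error and does not threaten the planned power. The size depends on the share of patients with eGFR 30–59, the eGFR effect and the spread between sites, none of which the documents give.

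**What to change.** Replace the primary-test sentence under Statistical analysis so that the composite is tested by CMH stratified by eGFR range and site, or by logistic regression on treatment, eGFR and site. Report a stratified (CMH) or standardized (logistic) risk difference with its 95% confidence interval. Choose one of the two as primary and keep the unadjusted chi-squared test as a sensitivity analysis. Record the change, with its date, before anyone has seen outcomes by arm, and carry it into the SAP.

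For rare secondary endpoints, reword the Fisher trigger to an expected count below 5.

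The cost is a sentence or two. Both stratification variables are already recorded at randomization, and N stays at 282.

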#### Enrollment

Screening will occur at the time of the initial appointment, at which time patients will be seen and assessed by the cardiac surgeon for consideration of aortic arch surgery. Patients who are booked for aortic hemiarch surgery with planned hypothermic circulatory arrest and ACP will be assessed for the aforementioned eligibility in the clinical trial. Once deemed eligible and written informed consent obtained, baseline neurological screening will be performed by trained personnel.

The following baseline information will then be collected at either this initial visit, or at the time of the preoperative anesthesia clinic visit (see SPIRIT Fig. 1):
Clinical information
Demographics—age, sexHTN (hypertension)DM (diabetes)DLP (dyslipidemia)NYHA class (New York Heart Association)Aortic stenosis
i.Graded: mild, moderate, severeAortic valve regurgitation
i.Graded: 1 to 4+CCS class (Canadian Cardiovascular Society)CAD (coronary artery disease)Previous history of strokePrevious history of TIA (transient ischemic attack)Carotid stenosisRenal diseasePVD (peripheral vascular disease)COPD (chronic obstructive pulmonary disease)Pulmonary HTNSmoking historyETOH use (ethanol)Congenital aortic diseaseAortic diameterEuroscore IIPhysical examination
Height (cm)Weight (kg)BMI (kg/m^2^)—body mass indexBSA (m^2^)—body surface areaLaboratory tests/investigations
Hb (g/L)—hemoglobinPlt (× 10^9^/L)—plateletINR (international normalized ratio)Cr (umol/L)—creatinineBUN (mmol/L)—blood urea nitrogeneGFR (ml/min/1.73m^2^)—estimated glomerular filtration rateHbA1C (%)—hemoglobin A1cNeurocognitive testing
NIHSS (The National Institutes of Health Stroke Scale)MOCA (Montreal Cognitive Assessment)MRS (Modified Rankin Scale)—only postoperatively in event of strokeBI (Barthel Index)Quality of life
SF-12 (Short Form) survey

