#### Secondary outcomes and definitions

Secondary endpoints will include:
Neurologic injury is divided into two major categories: temporary neurologic dysfunction (TND) or TIA and permanent neurologic dysfunction (PND) or stroke
TND or TIA—neurologic symptoms lasting < 24 h and without evidence of infarction
i.Neurological imaging has to be normal with resolution of all symptoms within 24 hPND or stroke—presence of either new focal (embolic stroke) or global (diffuse coma) deficits which persist for longer than 72 h
i.Positive radiographic evidence of infarction in the appropriate territory

In the event of a suspected neurological injury the clinical team will be alerted and the study neurologists will be consulted. Neurologic injury will be quantified using a combination of validated cognitive screening tests and neurologic imaging. Screening tests will be performed preoperatively and on postoperative days 2 ± 2, 6 ± 1 (or prior to discharge), and 60 ± 14 by trained personnel (study coordinator, study neurologist, study nurse practitioner). Note both BI and MRS scores will only be performed postoperatively in the event of a postoperative stroke and will occur at the same times as the follow up NIHSS/MOCA testing. These points in time have been chosen based on previous studies [26] that actively monitor for stroke post-cardiac surgery, as well as to allow for long-term follow up of patients post-stroke. Screening tests include:

c.The National Institutes of Health Stroke Scale (NIHSS)—highly predictive of hospital disposition and long-term stroke outcomes. Scores range from 0 to 42. It has been shown for each one-point increase in NIHSS, the likelihood of going home is significantly reduced [27–29]
i.0 = no strokeii.1–4 = minor strokeiii.5–15 = moderate strokeiv.15–20 = moderate/severe strokev.21–42 = severe strokevi.Study neurologists following serial NIHSS scores will determine whether there was a change in examination from previous exams and whether this change was because of a suspected stroke
For the purpose of this study, severe strokes are defined as NIHSS ≥ 10 [26]Clinically significant strokes are defined as a change in NIHSS ≥ 4
This is based on data which show NIHSS scores < 6 indicate a strong likelihood of hospital discharge, with good recovery, and no long-term deficits [28, 30]d.The Montreal Cognitive Assessment (MOCA)—highly sensitive in detecting executive dysfunction. Scores range from 0 to 30 [31]

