i.Delirium assessment will be performed using CAM
For a diagnosis of delirium by CAM, the patient must display:
Presence of acute onset and fluctuating course ANDInattentionAnd either one of:
Disorganized thinking ORAltered level of consciousnessii.Assessments will be performed on POD 2 ± 2 and 6 **±** 14.Death
All cause postoperative 60-day or in-hospital mortality5.Cardiopulmonary bypass (CPB) time (minutes)6.Bleeding rates to qualify for mediastinal re-exploration
Indication for exploration defined as postoperative mediastinal bleeding of [40, 41]:
i.500 ml in any one hourii.1000 ml in any 4-h periodiii.Or at surgeons discretion7.Incidence and quantity (number of units/patient) of perioperative blood transfusions
Defined as all intraoperative and postoperative transfusions up to POD 7 or discharge (whichever comes first)The transfusion of packed red blood cells (pRBCs) will adhere to the previously defined transfusion trigger strategy whenever possible without compromising patient safety
i.A liberal transfusion threshold of Hb < 95 g/L will be used intraoperatively and in the ICU, while a Hb < 85 g/L will be adhered to after transfer to the wardNumber of platelets, fresh frozen plasma (FFP), and cryoprecipitate will also be tabulated for the same time period
i.No transfusion triggers given and left to discretion of caring physician8.Prolonged mechanical ventilation
Defined as those requiring ≥ 48 h of mechanical ventilationMeasured in hours from time of admission to the ICU9.Perioperative myocardial infarction
Clinically diagnosed using a combination of electrocardiographic (new Q wave on 12 lead ECG) and biochemical (troponin I > 45 ng/L) markers or both10.Length of stay
ICU hoursHospital days11.Quality of life (SF-12) survey
A measure of perceived health (health-related quality of life) that describes the degree of general physical health status and mental health distress [42]Will be assessed preoperatively and on POD 60 ± 14

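### SF-12 has a preoperative score, but the stated comparison has no baseline adjustment and does not say whether follow-up or change is tested

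*Protocol article*

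**What the plan says.** All references are to the protocol article.

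- **Endpoint.** Secondary outcomes and definitions lists "Quality of life (SF-12) survey" as item 11 and gives its timing: "Will be assessed preoperatively and on POD 60 ± 14". Each patient should therefore have one score before surgery and one after.
- **Test.** Statistical analysis states that "continuous secondary endpoints will be analyzed using Students" t-test, or "Wilcoxon rank sum test if the data are not normally distributed". It gives no baseline term, and it does not say whether the variable is the day-60 score or the change from the preoperative score.
- **Other modelling.** The only regression in that section is for another purpose: "Exploratory multivariable logistic regression analysis will be performed to determine risk factors for neurologic and renal complications post-operatively". It does not estimate a treatment effect on SF-12.
- **Stratification.** Under Randomization, the factors are site and two eGFR ranges. Baseline SF-12 is not among them.
- **MOCA.** It is also measured before surgery (Enrollment) and repeated: "Screening tests will be performed preoperatively and on postoperative days 2 ± 2, 6 ± 1 (or prior to discharge), and 60 ± 14". Its stated role is different, however: "Neurologic injury will be quantified using a combination of validated cognitive screening tests and neurologic imaging". It is not a numbered secondary endpoint.

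**The concern.** A patient's health-status score before surgery usually predicts part of the score two months later. A two-group test on the follow-up score leaves that predictable part in the error term. A test on the change removes it by fixing the baseline slope at 1, which over-corrects whenever the true slope is smaller. ANCOVA estimates the slope from the data, so with equal variances at the two times its variance in large samples does not exceed that of either simpler test.

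What is at stake is the width of the confidence interval for quality of life. The trial was sized on a binary composite only, so nothing in the design secures precision for SF-12. Leaving the tested variable open also leaves two analyses possible under one sentence. They can give different estimates when the arms differ by chance at baseline.

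**Working it through.** **1. The plan's own figure.** The article gives no precision or power figure for SF-12. Its only sample size is 141 per arm (282 in total) for 35% versus 20%, alpha 0.05, power 80% and 5% loss. Taking alpha as two-sided, with unpooled variance:

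n = (1.96 + 0.84)² × (0.35 × 0.65 + 0.20 × 0.80) / 0.15² → 136 per arm.

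Inflating for loss gives 143 (× 1.05) or 144 (÷ 0.95) per arm, so 286 or 288 in total. That is within 3% of 282. The figure is used here only for the number evaluable: 141 × 0.95 ≈ 134 per arm.

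**2. Formulas.** Let r be the correlation between preoperative and day-60 SF-12. Assume equal standard deviations (SD) at both times and the same linear relation in both arms. Set the variance of the treatment difference from a t-test on the follow-up score to 1. Then:

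- t-test on change: 2(1 − r)
- ANCOVA: 1 − r²
- ANCOVA relative to change: (1 − r²) / [2(1 − r)] = (1 + r)/2

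**3. Results.** The documents do not give r, so the range is an assumption.

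| r | Follow-up t-test | Change t-test | ANCOVA | Reduction vs follow-up | Reduction vs change |
|---|---|---|---|---|---|
| 0.3 | 1.00 | 1.40 | 0.91 | 9% | 35% |
| 0.5 | 1.00 | 1.00 | 0.75 | 25% | 25% |
| 0.7 | 1.00 | 0.60 | 0.51 | 49% | 15% |
| 0.8 | 1.00 | 0.40 | 0.36 | 64% | 10% |

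The two readings lose precision at opposite ends of the range: the follow-up test when r is high, the change test when r is low. ANCOVA has the smallest variance in every row.

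**4. In terms of detectable difference.** With 134 per arm, two-sided alpha 0.05 and 80% power, the follow-up t-test detects (1.96 + 0.84) × √(2/134) = 0.342 SD. Multiplying by the square root of each variance above gives:

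| r | Follow-up | Change | ANCOVA |
|---|---|---|---|
| 0.3 | 0.342 | 0.405 | 0.327 |
| 0.5 | 0.342 | 0.342 | 0.296 |
| 0.7 | 0.342 | 0.265 | 0.244 |
| 0.8 | 0.342 | 0.216 | 0.205 |

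For an illustrative true difference of 0.3 SD, power is 69% with the follow-up t-test. With ANCOVA it is 73%, 81%, 93% and 98% at the four values of r. With the change t-test it is 55%, 69%, 89% and 97%.

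These figures are for the t-test. The Wilcoxon fallback also has no baseline term, but its efficiency was not calculated.

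**The case against.** **The baseline may be used after all.** A reader might infer that the plan throws the preoperative score away. The text does not support that: a t-test or rank test on change scores fits the sentence equally well. This objection stands, and it matters for size. At r = 0.7 the gain from ANCOVA is 49% against a follow-up test but only 15% against a change test. The smaller need for correction does not vanish, though, because ANCOVA is more precise under both readings.

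**MOCA.** It is tempting to extend the point to MOCA, which also has a preoperative score. MOCA appears as a screening test under neurologic injury, with a cut-off at 26, and nothing says its score will be compared between arms as a continuous outcome. The rule for continuous endpoints need not reach it, so the point is confined to SF-12.

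**Bias.** A reader might infer that baseline imbalance invalidates the comparison. It does not. Under randomisation the unadjusted test is unbiased, and its standard error already covers chance imbalance. What is lost is precision.

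**This belongs in the SAP.** Covariates are often left to the SAP, and the article announces one before analysis. That would answer a complaint about missing detail. Here, however, the article does name a test, and it is an unadjusted one. The SAP is to be written only after data collection is complete, so a later move to ANCOVA would be a change from published text. That is a reason to settle it early; it is not evidence that the SAP will get it wrong.

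**Conclusion.** The point holds for SF-12 as a matter of efficiency. The stated test is valid, but whichever variable it is applied to, it is less precise than ANCOVA on a baseline that is already collected. Over an assumed r of 0.3 to 0.8 the variance reduction is 9% to 64% if the follow-up score is tested, and 35% to 10% if the change is tested. These sizes rest on the assumed r and on equal SDs at the two times. The detectable differences also assume about 134 evaluable patients per arm; deaths or missing questionnaires beyond 5% would lower that number.

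The consequence is limited to one secondary outcome. The chi-squared analysis of the composite and the total of 282 do not depend on it.

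**What to change.** Before outcome data are seen, state in the protocol or SAP that the SF-12 physical and mental scores at day 60 ± 14 will each be compared by ANCOVA. The preoperative score, eGFR stratum and site would be covariates, and the adjusted mean difference would be reported with its 95% confidence interval. This also settles whether follow-up or change is analysed, since ANCOVA gives the same treatment estimate for both once baseline is in the model.

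State also whether MOCA scores will be compared between arms as a continuous measure. If so, adjust them for preoperative MOCA in the same way; if not, say so.

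The cost is a few lines of text. No new data, visits or patients are needed.
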